**Methods and analysis:**

360 participants recruited from three large Chinese medical hospitals in Zhejiang Province will be randomly divided into the integrative medicine rehabilitation (IMR) group and the conventional rehabilitation (CR) group in a 1:1 ratio. Participants in the IMR group will receive acupuncture and Chinese herbs in addition to basic Western medicine and rehabilitation treatment. The CR group will not receive acupuncture and Chinese herbal medicine. The assessment data will be collected at baseline, 4 and 8 weeks postrandomisation, and then at 12 weeks’ follow-up. The primary outcome is measured by the Modified Barthel Index. The secondary outcomes are the National Institutes of Health Stroke Scale (NIHSS), Fugl-Meyer Assessment, the mini-mental state examination and Montreal Cognitive, Hamilton's Depression Scale and Self-Rating Depression Scale, and the incidence of adverse events.

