### Randomisation and blinding

Randomisation was performed on Excel computer software for the study. The generated list of random numbers was printed, cut into small pieces, separated and placed into sequentially numbered, opaque, sealed envelopes. The envelopes were saved by special screeners. When a participant was included, the screeners opened the envelope to get the group information. Then the subject was informed whether they would be in the treatment group or control group, with or without acupuncture and Chinese herbs. All of the rehabilitation therapists, outcome assessors and data analysts are blinded to group assignments. However, it is impossible to make acupuncturists blinded, because they are trained to perform the treatment for participants of the IMR group.

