### The incidence of adverse events

Participants are to be questioned and report all adverse events (AEs) at each visit point, and all AEs reports will be recorded and assessed by the investigators. If serious AEs occur, the researchers should report to the principal investigator and ethics committee immediately, who will make a decision on whether or not the participant needs to withdraw from the study. If the participant suffered serious AEs, unbinding is permissible and procedure is followed for revealing a participant's allocated intervention during the trial. Compensation will be provided to those who suffer harm from trial participation.

In order to assess the safety of herbal medicine, we will perform the following tests on participants of the IMR group at baseline (week 0) and after treatment (week 12): routine blood test, routine urine test, routine faeces test, kidney function test and liver function test. In addition, investigators will ask subjects at each visit whether they have experienced allergies or gastrointestinal discomfort during the study period.

The AEs of acupuncture may include local bleeding, haematoma, pallor, sweating or dizziness, fainting during the acupuncture treatment, unbearable prickling or retained needle after treatment. The investigator should record the date of occurrence, time, degree, measurement related to the treatment and consequence.

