### Statistical analysis

Efficacy and safety analyses will be conducted according to the intention-to-treat (ITT) principle by a statistician blinded to group allocation. Missing values will be imputed by the last-observation-carried-forward method. All statistical analyses will be performed using Statistical Product and Service Solutions (SPSS) statistical package program (V.17.0, SPSS Inc, Chicago, Illinois, USA). The primary outcomes (MBI) and FMA will undergo ITT analysis including all the patients who are randomised. The analysis of cognitive impairment and emotional disorder will be made among the defined population of corresponding dysfunction. Continuous variables will be expressed as means with SDs. For normally distributed variables, two independent samples will be compared by independent sample t test. On the other hand, for abnormally distributed variables, non-parametric tests will be used and the data will be expressed as medians with ranges. A p value of less than 0.05 is considered as statistical significance. Safety analysis is based on the frequency of AEs relating to the treatment.

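### The safety analysis is restricted to treatment-related adverse events, which is narrower than the declared outcome and open to differential attribution between the arms

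*Protocol article*

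**What the plan says.** The Abstract (Methods and analysis) ends its list of secondary outcomes with "and the incidence of adverse events", and puts no condition of relatedness on it. The section The incidence of adverse events sets collection just as broadly: "Participants are to be questioned and report all adverse events (AEs) at each visit point". On handling, the same section provides that "all AEs reports will be recorded and assessed by the investigators". The Statistical analysis section then narrows this: "Safety analysis is based on the frequency of AEs relating to the treatment". The same section places safety under the intention-to-treat principle, in the hands of a statistician blinded to allocation.

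On who knows the allocation, Randomisation and blinding says of participants: "Then the subject was informed whether they would be in the treatment group or control group, with or without acupuncture and Chinese herbs". Of acupuncturists it says that "it is impossible to make acupuncturists blinded". The blinded roles are listed: "All of the rehabilitation therapists, outcome assessors and data analysts are blinded to group assignments". Investigators who assess AEs are not in that list, and they are not described as unblinded either.

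On exposure, the section Conventional rehabilitation group says that the CR arm has no acupuncture and no herbs, only basic Western medical care and rehabilitation. Laboratory safety testing is specified for one arm: "we will perform the following tests on participants of the IMR group".

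**The concern.** The outcome declared, the data collected and the analysis stated do not match. The first two cover all AEs; the third keeps only those judged to relate to treatment. This is a stated rule and not a detail left out, so an analysis plan that followed it would carry the restriction forward.

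Randomisation protects a comparison of all AEs. It does not protect a comparison of AEs that have passed a judgement which may depend on the arm. Two features make that likely here. Acupuncture and herbs, the candidate causes under study, exist in one arm only. And the participants who report events, like the acupuncturists, know the allocation.

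The error can run either way. Events equally common in both arms may be called related more often in IMR, which gives a false signal of harm. Or a real excess in IMR may be put down to the stroke or to Western medicine and drop out of the analysis. For an add-on to standard care, a comparison of all events by arm is what would show such an excess, and the stated analysis omits it.

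**Working it through.** **Comparing the statements**

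| Step | What is covered | Where |
|---|---|---|
| Outcome | Incidence of AEs, unrestricted | Abstract, Methods and analysis |
| Collection | All AEs, every visit, no limit to one arm | The incidence of adverse events |
| Laboratory tests | IMR arm only | The incidence of adverse events |
| Analysis | AEs relating to the treatment | Statistical analysis |

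The term treatment has two readings in CR. If it means acupuncture and herbs, CR is near zero by construction. If it means whatever the arm receives, CR can have related events, but IMR still has more candidate causes for any given event.

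**Size, on assumptions**

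The plan gives no AE rate and no safety power, so there is no figure of its own to reproduce. From the documents: 360 participants at 1:1, so n = 180 per arm. Assumed: the same true all-cause AE rate p in both arms, at most one AE counted per patient, a share a1 of IMR events called related (0.50), and a share a0 of CR events called related (varied).

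Related rates: p1 = p × a1 and p0 = p × a0. With m = (p1 + p0)/2, the chance that a two-sided 5% comparison of proportions finds a difference is approximately

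Φ{ [ (p1 − p0) − 1.96 √(2m(1 − m)/n) ] / √([p1(1 − p1) + p0(1 − p0)]/n) }.

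Example: p = 0.20, a0 = 0.25. Then p1 = 0.10, p0 = 0.05 and m = 0.075. The null standard error is √(2 × 0.075 × 0.925/180) = 0.0278, and 1.96 × 0.0278 = 0.0544. The alternative standard error is √((0.0900 + 0.0475)/180) = 0.0276. So Φ((0.0500 − 0.0544)/0.0276) = Φ(−0.16) ≈ 0.44.

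Each cell gives expected related events in IMR vs CR, then the chance of a false difference:

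| True AE rate | a0 = 0.25 | a0 = 0.10 | a0 = 0 |
|---|---|---|---|
| 10% | 9 vs 4.5; 24% | 9 vs 1.8; 61% | 9 vs 0; 86% |
| 20% | 18 vs 9; 44% | 18 vs 3.6; 90% | 18 vs 0; 99% |
| 30% | 27 vs 13.5; 62% | 27 vs 5.4; 98% | 27 vs 0; about 100% |

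If a0 = a1 = 0.50, the counts are equal (18 vs 18 at a 20% rate) and nothing is distorted. The result is driven by the gap in attribution.

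**The opposite error**

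Assume true rates of 30% in IMR and 20% in CR: 0.30 × 180 = 54 against 0.20 × 180 = 36, an excess of 18. Suppose all 18 extra events are judged unrelated, and half of the other 36 in each arm are called related. The filtered comparison is then 18 vs 18. For all AEs, m = 0.25, and the formula gives Φ((0.1000 − 0.0895)/0.0453) ≈ 0.59. An excess with about a 59% chance of being detected would vanish from the stated analysis.

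**The case against.** The strongest reply is that one sentence of a condensed article does not show that other AEs will go unreported. Tables of all AEs and rules for causality are commonly left to the analysis plan. The reply is right that the absence of such detail is no fault. But the sentence is not silent: it says what the safety analysis rests on, and that differs from the declared outcome.

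Other replies limit how far the point goes.

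- A reader might infer that this is an open trial. The documents call it assessor-blinded and blind the rehabilitation therapists, outcome assessors and data analysts. Only participants and acupuncturists are clearly open. The blinded statistician, however, cannot undo attribution bias already in the data.
- A reader might infer that unblinded investigators decide relatedness. The article says that they record and assess AE reports; it does not say who judges causality or whether that person is blinded. It also has case report forms filled in by assessors, and the provision for unblinding after a serious AE suggests that some staff start out blinded.
- A reader might infer that CR can have no related events. That holds under only one reading of an undefined term.
- A reader might conclude that the arms cannot be fairly compared on safety. That is true of the filtered analysis, not of the data: reported AEs are collected without restriction to one arm, so they can be compared, laboratory findings apart.
- The IMR-only laboratory tests have a stated purpose, the safety of the herbal medicine, and no between-arm laboratory comparison is claimed. They matter here only because an abnormality found by these tests could enter an AE count in one arm alone.
- The article names no between-arm test for AEs. The percentages above show what such a comparison would do; they are not a result that the plan commits to.

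**Conclusion.** The point holds as a mismatch with a foreseeable bias: the stated safety analysis is narrower than both the declared outcome and the data collected, and its filter depends on a judgement that is open to knowledge of the arm. The wording and the difference in exposure are established from the document. That attribution will in fact differ is a risk, since the article does not state who decides on relatedness or whether that person is blinded.

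The size cannot be fixed from the documents. Over assumed AE rates of 10% to 30%, with half of IMR events called related and between none and a quarter of CR events, the chance of a false difference runs from about 24% to nearly 100%. It falls back to the nominal level if attribution is equal. The severity is moderate: a secondary outcome is affected, the primary analysis of the Modified Barthel Index is untouched, and the data needed for the remedy are already planned.

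**What to change.** In Statistical analysis, replace the safety sentence so that:

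1. the main safety analysis is the incidence of all AEs and of all serious AEs by randomised arm, regardless of attribution, with the risk difference and its 95% confidence interval;
2. treatment-related and needle-specific events are shown as supplementary description, with a statement of what counts as the treatment in each arm, who judges relatedness and whether that person is blinded;
3. the IMR-only laboratory results are reported as within-arm data, with no between-arm conclusion drawn from them.

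The cost is a reworded paragraph and one extra table. No new data are needed, since all AEs are already to be asked about and recorded at each visit.

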## Discussion

China’s extensive clinical experience in the use of TCMs in stroke therapy indicates that TCM preparations are effective. More than 100 traditional medicines are currently in use for stroke therapy in China.^23^ However, insufficient good-quality evidence on the effects of TCM in ischaemic stroke exists on the primary outcome.^24^ One possibility for lack of evidence in the literature could result from the significant clinical and methodological heterogeneity, preventing effective meta-analysis techniques. No meta-analysis has been performed and thus no cumulative results obtained by pooling RCT data exist.^25^ Further randomised controlled trials are justified.

Acupuncture is recommended for stroke according to the WHO.^26^ Literature reviews have demonstrated the safety of acupuncture, legitimising its ethical use for patients, without causing harm.^7^ Despite its safety, the limited availability of rigorous RCTs and the lack of research available on complementary and alternative medicine treatments such as acupuncture, create a controversial opinion on its benefit for specific disease outcomes.^7^
^27^
^28^ This lack of evidence necessitates additional RCT study on the clinical efficacy of IM on stroke outcomes.

Complementary or alternative medicine such as acupuncture and Chinese medicine, or IM, has become increasingly prevalent and popular, not only in China, but also worldwide.^29^
^30^ Integrated traditional Chinese and Western medicine for stroke rehabilitation is widely used in China, making it an ideal setting to study stroke treatment protocols. The integrated approach is forming characteristics of some of China's stroke treatment modalities, which can be observed as a model for the rest of the world.^31^ In China, many patients with stroke receive basic Western medicine and rehabilitation as well as acupuncture and Chinese medicine during hospital stays. So we are conducting this clinical trial, which is close to the actual treatment strategy in China, to objectively evaluate the clinical efficacy. Syndrome differentiation and treatment is the essence of Chinese medicine, so in our study, Chinese herbal prescriptions for patients with stroke are clarified. Four types of herbal medicine are most common in the clinic according to syndrome differentiation. The acupuncture programme traditionally includes scalp acupuncture and body acupuncture and, in addition, some acupoints are selected according to the patient’s dysfunction and also syndrome differentiation. Under strict quality control, this study could potentially confirm whether or not IM is an effective adjunct to the standard rehabilitation therapy for ischaemic stroke. Our study may also assess the efficacy of IM in promoting the recovery of motor dysfunction, cognitive impairment and emotional disorder.

## Conclusion

This trial has been designed to provide robust data on the efficacy of IM for patients with ischaemic stroke. It is also expected to clarify whether or not IM is effective for motor, cognitive or emotional disorder after stroke.
